**Table 1 Tab1:**
[figure not shown]
Schedule of enrolment, interventions, and assessments

### Primary endpoint

Primary endpoint is the level of pain measured on the visual analogue scale (VAS) after 120 h of SCS. VAS is a globally used instrument where patients rank their pain on a scale from 0 to 100. “0” corresponds to the pain-free state and “100” to the maximum imaginable state of pain. VAS is the most prevalent endpoint for studies involving SCS. In addition to VAS rating, patients are asked to assess which SCS program was most beneficial to them during their final visit at day 36.

### Secondary endpoints

Secondary endpoints include self-assessment through four validated questionnaires: pain quality as determined by painDETECT questionnaire (painDETECT), quality of life as determined by Quality of Life EQ-5D-5L questionnaire (EQ-5D-5L), anxiety perception as determined by the German version of the Hospital Anxiety and Depression Scale (HADS-D), and physical restriction as determined by the Oswestry Disability Index (ODI). All questionnaires are standardized and well established in SCS research [10–13].

In addition, demographic and study-related data are collected by the respective study centers during the screening visit (immediately after consent/inclusion of study participants) and during the final visit, which coincides with the regular clinical follow-up on day 36 of the trial. Data include electrode position (position of the distal electrode tip), medical history, potential complications related to SCS implantation, and total hours of stimulation per day.

### Patient timeline and trial visits

Routine implantation of the wireless SCS device occurs prior to the trial and as part of regular patient care (day 0). On days 1 and 2, patients are informed about the trial, and upon consent, inclusion and exclusion criteria are reviewed. Provided that all inclusion criteria and no exclusion criteria are met, an independent technician programs the previously randomized order of the four different SCS modes (“burst,” “1 kHz,” “1.499 kHz,” and “placebo”) into the SCS hardware. To patients, these four SCS modes are only known as programs 1, 2, 3, and 4. All patients are thoroughly instructed in the general handling of the SCS device. For a total of 7 days after implantation, SCS is switched off to wash out any potential effect caused by electrode placement during the preceding SCS surgery.

After this first washout phase (day 7) and with SCS switched off, patients are contacted by the respective study center. Patients are asked to assess pain on the VAS and are requested to fill out four questionnaires (painDETECT, EQ-5D-5L, HADS-D, and ODI). Time needed to complete the questionnaires is estimated at 1 h. Patients are instructed to activate the first stimulation mode immediately after completing the questionnaires. Specifically, patients are instructed to use each stimulation mode for 120 h and to stimulate at least 8 h per day. In addition, patients are asked to record daily stimulation durations in a patient journal, i.e., since it is not possible to record stimulation times with the wireless SCS device directly, patients are handed a diary after enrolment. This diary contains one page for every single day of the intervention. Study participants are instructed to record each time during the day when SCS was switched on and when SCS was switched off. If there are multiple periods of SCS during a day, patients are instructed to record stimulation times for each SCS period.

After 120 h of stimulation with the first stimulation mode (day 12), patients are contacted by the respective study center and asked to assess pain on the VAS and to fill out the four questionnaires (painDETECT, EQ-5D-5L, HADS-D, and ODI). After completing the questionnaires, patients are instructed to switch off stimulation. Now follows a washout phase of 70 h, during which stimulation remains switched off.

After the washout phase (day 15) and with stimulation still switched off, patients are contacted by the respective study center and asked to assess pain on the VAS and to fill out the four questionnaires (painDETECT, EQ-5D-5L, HADS-D, and ODI). Patients are then instructed to activate the second stimulation mode immediately after completing the questionnaires. This procedure (stimulation for 120 h, questionnaires, 70 h of washout phase, questionnaires, activation of the next SCS modality) is repeated exactly until the patient has been subjected to all four SCS modalities.

On day 36 (after 120 h of stimulation with the fourth stimulation modality), patients present for an outpatient appointment for regular clinical follow-up at the respective trial site, which coincides with the last study visit. Patients are asked once more to assess pain on the VAS and to fill out the four questionnaires (painDETECT, EQ-5D-5L, HADS-D, and ODI) and are asked to assess which SCS program was most beneficial to them overall. An independent technician performs a final paresthesia-inducing test stimulation to confirm that the pain area is still covered by at least 90%. The patient then chooses the preferred stimulation mode.

### Data management

Data management is carried out according to the Standard Operating Procedures (SOPs) of the Institute for Medical Biometry and Informatics (IMBI) Heidelberg. All demographic and trial-related data collected within the scope of this trial are entered by the respective trial sites into an electronic Case Report Form (eCRF) implemented in the Research Electronic Data Capture (REDCap™) system (www.project-redcap.org). Completeness, validity, and plausibility of the data are checked by a data validation program. Questionnaires filled out by patients in paper form as part of the trial are forwarded by trial sites to the IMBI for data entry. Double data entry will be performed where applicable.

### Sample size calculation

Sample size calculations are based on a previous SCS study protocol by Kriek et al. [14]. Analogous to this study protocol, we chose a minimal detectable effect size of 0.15 (i.e., 15%) on our primary outcome parameter, arriving at a required sample size of 48 patients with a power of 82.9% and a significance level of 0.05. Due to the statistical design of our trial, it will not be possible to censor or replace study participants after study termination. For this reason, a termination/dropout rate of 20% was assumed for sample size calculations and the total number of patients increased from *n* = 48 to *n* = 60. In the case of a drop in the number of trial participants below the minimum number of *n* = 48, the study protocol provides for the replacement of these participants by the recruitment and inclusion of additional study participants. To reduce the likelihood of missing data, four measures will be implemented: (1) Patients will be sensitized by study personnel and on several occasions to the fact that adherence to the study protocol is indispensable for study success. Date and time of each prospective study visit are explained to study participants and entered into a calendar which patients receive immediately after enrolment. (2) Study participants will be contacted via phone by study centers each time they have to assess stimulation effects and have to fill out questionnaires. During these phone calls, patients will be sensitized again to the fact that missing data might compromise the study. If a study participant cannot be reached within an agreed period of time, he or she will be made aware again during the first subsequent contact that a complete and precise procedure is essential for the success of the individual study. (3) A data validation plan was implemented. This plan generates automatic and instantaneous queries if data entry by study personnel is incomplete or implausible (e.g., date of intervention predates date of enrolment). (4) During the last study visit, study personnel screens each patient’s questionnaires to identify missing data. If missing patient data is identified and retrospective data collection does not compromise study results, patients are asked to provide missing data (e.g., patients will be asked to provide a missing name, a missing date, or a missing medication name but will not be asked to “remember” how much pain relief they had during a particular stimulation cycle). Sample size calculation was done using PASS Vs. 16.03 and was based on previous work by Chow et al. [15].

### Analysis variables and statistical methods

All variables will be reported by tabulation of the measures of the empirical distributions. According to the scale levels of the variables, means, standard deviations, medians, and minimum and maximum or absolute and relative frequencies will be reported. Descriptive *p* values of the corresponding statistical tests (*t* test in the case of continuous data, chi-square test for categorical data) and confidence intervals will be reported. The primary endpoint, pain perception on the VAS, will be evaluated using a linear mixed model with sequence, period, and treatment as fixed factors and patient as random factor. Statistical analysis will be done with SAS Vs. 9.4 or higher and the procedure *proc mixed*.

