### Assignment of intervention, randomization, and blinding

The study is planned as a fourfold crossover study using a Williams design. In a crossover design, patients are not randomly assigned to treatments, but rather treatment sequences are randomized. Such a crossover design avoids inter-patient variability and reduces the required sample size to power this trial. On the other hand, it increases the length of the intervention for each individual patient and thus, ultimately, might negatively influence patient compliance.

Since some part of the SCS effect observed at early stages of therapy may be the result of a placebo effect, and some studies have reported placebo effects comparable to SCS effects [9], the study also includes a placebo control, i.e., a time interval in which there is no stimulation and which should be indistinguishable from paresthesia-free SCS.

Each patient is treated with four SCS modalities (“burst,” “1 kHz,” “1.499 kHz,” and “placebo”). All stimulation sequences are generated at the beginning of the trial, and each patient will be randomly assigned to one of 24 unique treatment sequences. An independent technician will program the SCS modalities as well as the order of the different stimulation modalities into the wireless SCS control hardware prior to the intervention.

A randomization list was generated prior to trial initiation. The designated trial statistician had no access to the lists and was not involved in the generation of the randomization list. A randomization number (1–500) was randomly assigned to one of the 24 unique treatment sequences (e.g., randomization #1: “1 kHz”-“placebo”-“1.499 kHz”-“burst,” randomization #2: “burst”-“placebo”-“1 kHz”-“1.499 kHz”). This list was further divided into blocks of equal length so that each participating center would receive a list of randomized sequences and a matching number of sealed envelopes containing one treatment sequence per envelope (e.g., center #1 would receive randomization numbers and the corresponding treatment sequences 1–50 as well as 50 sealed envelopes with treatment sequences 1–50, center #2 would receive randomization numbers and the corresponding treatment sequences 51–100, as well as 50 sealed envelopes with treatment sequences 51–100).

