### Intervention

Seven days after implantation of the wireless SCS device, patients are contacted by the respective study center and asked to quantify pain on the visual analogue scale (VAS) and to complete the study questionnaires (Table 1). Patients are then requested to activate the first SCS modality which is known to them only as program 1. One hundred twenty hours after activation of the first SCS modality, patients are contacted once more by the respective study center and asked to quantify pain on the VAS and complete the study questionnaires. Patients are then requested to switch off SCS. After a washout period of 70 h, patients are contacted again by the respective study center. Once more, patients are asked to quantify pain on the VAS and complete the study questionnaires. Patients are then requested to activate the second stimulation program which is known to them only as program 2. This procedure (stimulation, test battery, washout phase, test battery, activation of the next SCS modality) is repeated until patients have been consecutively treated with all four SCS modalities.

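### The primary model omits the stimulation-off VAS rated before each of the four periods; the analysis stays valid but may be less precise than the collected data allow

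*Protocol article*

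**What the plan says.** The design is a "fourfold crossover study using a Williams design" with four modalities, four periods and 24 sequences (Protocol article, Assignment of intervention, randomization, and blinding). The outcome is a raw post-treatment level: "Primary endpoint is the level of pain measured on the visual analogue scale (VAS) after 120 h of SCS" (Primary endpoint).

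A stimulation-off rating precedes every period. For period 1: "After this first washout phase (day 7) and with SCS switched off, patients are contacted by the respective study center", with a VAS rating and four questionnaires (Patient timeline and trial visits). For period 2: "After the washout phase (day 15) and with stimulation still switched off, patients are contacted by the respective study center and asked to assess pain" (same section). The Intervention section says the same, "After a washout period of 70 h, patients are contacted again by the respective study center" and "Once more, patients are asked to quantify pain on the VAS and complete the study questionnaires", and extends it to the remaining periods: "This procedure (stimulation, test battery, washout phase, test battery, activation of the next SCS modality) is repeated until patients".

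The section Analysis variables and statistical methods lists the terms of the primary model: "linear mixed model with sequence, period, and treatment as fixed factors and patient as random factor". No pre-stimulation VAS is among them, and the article gives these ratings no other role in the primary analysis.

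**The concern.** With a random patient effect, stable differences between patients drop out of the treatment contrasts. Their standard errors then depend on how much one patient's pain varies from period to period. The sequence factor cannot reduce that variation, because it is constant within a patient. The pre-period VAS can: if a patient whose pain is unusually high just before a program also tends to rate higher 120 h later, the period baseline explains part of the residual.

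The ratings are already being collected, and each test battery is estimated to take the patient about an hour. At stake is some power for the primary comparison in a trial whose centers each expect 2-3 patients a year.

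**Working it through.** **Inputs from the article.** Four treatments, four periods, 24 sequences; N = 48, power 82.9%, significance level 0.05, effect 0.15, dropout 20% (Sample size calculation); rating days (Patient timeline and trial visits).

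**Assumptions, because the article does not give them.** The effect of 0.15 is read as 15 points on the 0-100 VAS. The test is two-sided and pairwise, without multiplicity adjustment. The SD is back-solved in step 2. The correlation r, between pre-period and 120 h VAS within a patient after the patient effect is removed, is taken from 0 to 0.5.

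**1. Rating days.** Five days on and about three off from day 7 give 7, 12, 15, 20, 23, 28, 31, 36. The article names days 7, 12, 15 and 36; the others follow. The pre-period ratings fall on days 7, 15, 23 and 31.

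**2. The plan's own figures.** 48 / (1 - 0.20) = 60 reproduces. The 82.9% cannot be reproduced without an SD. Back-solving: SD of the difference = 15 × √48 / (1.960 + 0.950) = 103.9 / 2.910 = 35.7 points, so the within-patient SD is 35.7 / √2 = 25.3.

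**3. Contrast without baseline.** SE = 35.7 / √48 = 5.15. Power = Φ(15 / 5.15 - 1.960) = Φ(0.95) = 82.9%.

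**4. Contrast with the within-patient baseline deviation.** The variance is multiplied by 1 - r²; the equivalent N is 48(1 - r²), rounded up.

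| r (assumed) | Variance factor | SE | Power | Equivalent N |
|---|---|---|---|---|
| 0 | 1.00 | 5.15 | 82.9% | 48 |
| 0.2 | 0.96 | 5.05 | 84.4% | 47 |
| 0.3 | 0.91 | 4.92 | 86.2% | 44 |
| 0.4 | 0.84 | 4.72 | 88.8% | 41 |
| 0.5 | 0.75 | 4.46 | 91.9% | 36 |

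**5. Simulation check.** The setting was 48 patients, each of the 24 sequences twice, and within-patient SD 24.75 (SD of the difference 24.75 × √2 = 35.0). At r = 0 the adjustment costs about 1% in variance. At r = 0.3 it removes about 9% (power about 84% to 87%), and at r = 0.5 about 24% (about 85% to 92%).

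**6. The form of adjustment matters.**
- A change score multiplies the variance by 2(1 - r). At r = 0.3 that is 1.4, and power falls to 69.1%. It breaks even only at r = 0.5.
- The raw baseline as a single covariate beside the random patient effect mixes between- and within-patient slopes. With random-intercept data the simulated variance ratio is 1.04, 1.11 and 1.24 at an intraclass correlation of 0.3, 0.5 and 0.7.
- Splitting the baseline into patient mean and period deviation avoids both losses.

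**7. Carry-over.** Suppose three active programs each lower VAS by 15 and 40% carries over, so a preceding active program shifts the next pre-period rating by -6. Over all 24 sequences an active period follows another active in 1/2 of cases and a placebo period follows an active in 3/4. The mean baseline shift is -6 × 1/2 = -3.0 before active and -6 × 3/4 = -4.5 before placebo, a difference of +1.5. With a slope of 0.4 (r = 0.4, equal SDs), adjustment moves the active-placebo estimate by -0.4 × 1.5 = -0.6.
- Carry-over gone by 120 h: -15.0 unadjusted becomes -15.6, a slight overcorrection.
- Carry-over of the same size persisting to 120 h: -15 + 1.5 = -13.5 unadjusted becomes -14.1, a partial correction.

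Simulations gave the same shift of about 0.6 in both cases. At r = 0 there is no correction at all.

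**The case against.** The stated model is the conventional one for a crossover trial and gives valid contrasts for the stated endpoint. A baseline covariate is an efficiency refinement, and an analysis plan that is not shown may already contain it. The gain also rests on an unknown: under the random-intercept structure that the model implies, r = 0 and nothing is lost. With serially correlated pain the simulated variance ratio ranged from 0.70 to 1.01, but only from 0.98 to 1.01 when half the within-patient variance was visit-to-visit noise. The larger gains need r of 0.4 to 0.5 between single ratings five days apart, with a program started in between. Finally, the baselines of periods 2-4 are taken after randomization and follow the previous modality.

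Most of this stands, and it limits the point. A reader might infer that the trial certainly loses precision, or that the primary analysis is biased; the article supports neither. A reader might also infer that the baselines correct for incomplete washout. Step 7 shows that this depends on whether carry-over lasts to 120 h, and the Discussion itself says the data on washout length are insufficient. Extending the remedy to the questionnaires would go too far as well: they are exploratory, and the article states no model for them.

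Two things do not fall. The article lists the model terms, so this concerns a stated choice rather than a detail left unsaid. And the trade-off is lopsided: about 1% of variance if r = 0, against a useful gain if r is about 0.3 or more.

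**Conclusion.** The point holds as one of efficiency, not validity. Four stimulation-off VAS ratings per patient are collected and the stated primary model uses none of them. Adjusting in mean-and-deviation form would reduce contrast variance by about r squared: nothing at r = 0, about 9% at 0.3, about 25% at 0.5. Power would go from roughly 83-84% to about 86-87% at r = 0.3 and about 92% at r = 0.5. These figures rest on an assumed SD of the difference of about 35 points, a 15-point effect, a two-sided 0.05 test and an assumed r; the article states neither SD nor r. The effect of adjustment under carry-over can go either way and is small in the case examined (about 0.6 points at 40% carry-over and r = 0.4).

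**What to change.** Before unblinding, add two covariates to the primary VAS model: the patient's mean pre-period VAS, and each period's deviation from that mean. Do not use the raw baseline alone, and do not switch to a change score. With complete data the deviation carries the gain; the mean keeps the between- and within-patient slopes apart. Set a rule in advance for a missing pre-period rating, for example the mean of the available ratings with that period's deviation set to 0. Report the model without the two terms as a sensitivity analysis, and say in the plan that carry-over confined to the pre-period rating would shift the adjusted estimate slightly.

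The cost is two model terms, one or two degrees of freedom, about 1% of variance if r is zero, and the carry-over sensitivity just named. No new data are needed.

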### Study-related risks

Since implantation of the wireless SCS device takes place independently and prior to study participation, rates of wound infection and technical failure are not affected by study participation.

### Clinical data monitoring

Monitoring is carried out by the Study Center of the German Surgical Society (SDGC) according to the SDGC’s SOPs and in compliance with the ICH-GCP guideline (E6). Monitoring focuses on patient safety and patient rights, on compliance with the study protocol as well as on data validity. All investigators must provide access to the SDGC’s independent monitors to study specific data and allow on-site visits before, during, and after study completion. Investigator site files are created and made available to the centers.

## Discussion

The PARS-trial will compare the clinical effectiveness of the three most relevant SCS paradigms in individual patients. To our knowledge, the wireless SCS device employed in this study is the only device that can reproduce all relevant paresthesia-inducing and paresthesia-free SCS modalities. Our crossover study design seizes the advantage of wireless SCS, namely the possibility to test several different SCS modalities in one and the same patient, thus avoiding inter-patient variability and reducing the required sample size to power this trial.

But even with this wireless SCS technology, it will be extremely difficult to compare paresthesia-inducing and paresthesia-free SCS modalities in a blinded fashion. The PARS-trial is thus restricted to paresthesia-free SCS modalities. In addition, patients are required to recharge their SCS device every 6 h, preventing patients from drawing conclusions about individual stimulation modalities based on different battery runtimes.

To our knowledge, there is not enough systematic data to assess the optimal washout period. A recent review by Duarte et al. [9] identified 12 RCTs of SCS. Washout periods were heterogeneous: 4 RCTs did not include a washout period between SCS modalities. In studies that included a washout period, periods included 15 min, 12 h, 2 days, and 1 week. Given such uncertainty regarding the proper length of the washout period, we considered a 70-h washout period to be a good trade-off between a conservative approach and an appropriate length of the intervention period. A washout period lasting 70 h instead of 72 h was chosen to avoid time shifts during the intervention period. Time required to fill out questionnaires was estimated at 1 h. Since one round of questionnaires would be filled out after 5 days of SCS and one round of questionnaires after the subsequent washout period, the next SCS cycle would start 72 h + 2 h later in the alternative scenario, i.e., each subsequent SCS cycle would start 2 h later during the day (e.g., first SCS cycle starts at 4 pm, second SCS cycle starts at 6 pm, and third SCS cycle has to start at 8 pm at night). To keep times consistent for trial participants and to make it easier for them to integrate SCS times into their daily routines, we reduced the washout period to 70 h. Accordingly, and from a trial participant’s perspective, SCS and washout periods would thus always start at the same time during the day.

Since the wireless SCS device does not record stimulation duration, the PARS study protocol will rely on patients’ compliance to stimulate an average of 8 h a day and record stimulation times in a patient’s diary. An average of 8 h per day was chosen based on our previous experience with the wireless SCS system. We recently evaluated patients suffering from therapy-resistant neuropathic pain, who were implanted with a wireless SCS system at our institution [16]. Patients reported that longer stimulation periods were difficult to integrate in their daily (working) routines and very few of them required SCS at night.

From these results and from current practice, we also concluded that many patients who benefited from wireless SCS already benefited within 72 h, even though, in several cases, the full SCS benefit only materialized after several weeks. While extending each stimulation period in the abovementioned trial from 5 days to several weeks would be technically feasible, we would also anticipate a strong and negative effect on patient compliance. Altogether, we are convinced that 5 days of SCS per stimulation paradigm is the best trade-off between response times experienced in our pilot study and an appropriate length of the intervention period.

In our experience, optimal electrode position (i.e., placement of the distal electrode tip) ranges from Th8 to Th12 for most patients. Thus, this range reflects a compromise between the need for a standardized electrode localization and the need to adapt epidural position to individual patients in order to achieve high (≥ 90%) pain coverage.

An important feature in our study protocol is the washout period between each stimulation modality. There is little knowledge regarding optimal washout periods after initial SCS implantation and after SCS treatment. For our study protocol, we have thus chosen a conservative approach, i.e., 7 days of washout period after initial implantation and 3 days after each SCS cycle.

Finally, during a recent evaluation of the wireless SCS system which was conducted at our institution [16], we had the opportunity to assess questionnaire fatigue in our patients. Based on this pilot experience, it seemed feasible to conduct repeated surveys over a 35-day intervention period.

